#### **Secondary endpoints**

Important secondary endpoints are:

- Body weight
- Length
- Head circumference

These will be modelled by a linear mixed effects model. Subject will be used as a random factor, and *GA* and *treatment* will be used as fixed factors.

## 11.2 Study Populations

All available subjects will be used in the data summaries and the listings of subject data. If a subject is regarded as non-evaluable this subject may be listed separately and not included in the summary statistics.

## 11.3 Background and Demographic Characteristics

The background and demographic variables will be displayed in per subject listings. The quantitative variables will also be summarized by means, standard deviations and medians. The qualitative variables will be displayed in frequency tables.

## 11.4 Analysis of Efficacy Parameters

### Fatty acid analysis

Serum concentrations of fatty acids will be reported for the child and mother and displayed in per subject listings and graphs. The efficacy parameters will be displayed in per subject listings and summarized by means, standard deviations and median values.

### ROP evaluation

The ophthalmologic assessment will be performed with strict criteria according to general Swedish Guidelines issued by the Swedish Ophthalmological Society: The Guidelines are available at following link: [www.swedeye.org/SOTA/rop/SOTA-ROP\\_2006.pdf](http://www.swedeye.org/SOTA/rop/SOTA-ROP_2006.pdf).

The evaluation of ROP stage 3 or more will be assessed by retinal examination by a trained ophthalmologist and will be performed in a blinded fashion i.e. the ophthalmologist will be unaware of whether or not the infant is participating in the clinical study.

## 11.5 Analysis of Safety/Tolerability

Physical examination, MRI and the results of retinal examination will be displayed in per subject listing.

The vital signs and laboratory measurements will be listed per subject and illustrated graphically as levels per time-point (as per Table 1, page 11) by each subject. The measurements will also be summarized by descriptive statistics.

Adverse events will be displayed in per subject listings.

--- ❖ ---

## APPENDIX I

### 1330 WORLD MEDICAL ASSOCIATION DECLARATION OF HELSINKI

#### 1331 Ethical Principles for Medical Research Involving Human Subjects

1332 Adopted by the 18th WMA General Assembly Helsinki, Finland, June 1964 and amended by  
1333 the:

1334 29th WMA General Assembly, Tokyo, Japan, October 1975

1335 35th WMA General Assembly, Venice, Italy, October 1983

1336 41st WMA General Assembly, Hong Kong, September 1989

1337 48th WMA General Assembly, Somerset West, Republic of South Africa, October 1996

1338 52nd WMA General Assembly, Edinburgh, Scotland, October 2000

#### 1339 A. INTRODUCTION

- 1340 1. The World Medical Association has developed the Declaration of Helsinki as a  
1341 statement of ethical principles to provide guidance to physicians and other partici-  
1342 pants in medical research involving human subjects. Medical research involving hu-  
1343 man subjects includes research on identifiable human material or identifiable data.
- 1344 2. It is the duty of the physician to promote and safeguard the health of the people. The  
1345 physician's knowledge and conscience are dedicated to the fulfillment of this duty.
- 1346 3. The Declaration of Geneva of the World Medical Association binds the physician  
1347 with the words, "The health of my subject will be my first consideration," and the In-  
1348 ternational Code of Medical Ethics declares that, "A physician shall act only in the  
1349 subject's interest when providing medical care which might have the effect of weak-  
1350 ening the physical and mental condition of the subject."
- 1351 4. Medical progress is based on research which ultimately must rest in part on experi-  
1352 mentation involving human subjects.
- 1353 5. In medical research on human subjects, considerations related to the well-being of the  
1354 human subject should take precedence over the interests of science and society.
- 1355 6. The primary purpose of medical research involving human subjects is to improve  
1356 prophylactic, diagnostic and therapeutic procedures and the understanding of the aeti-  
1357 ology and pathogenesis of disease. Even the best proven prophylactic, diagnostic, and  
1358 therapeutic methods must continuously be challenged through research for their effec-  
1359 tiveness, efficiency, accessibility and quality.
- 1360 7. In current medical practice and in medical research, most prophylactic, diagnostic and  
1361 therapeutic procedures involve risks and burdens.
- 1362 8. Medical research is subject to ethical standards that promote respect for all human be-  
1363 ings and protect their health and rights. Some research populations are vulnerable and  
1364 need special protection. The particular needs of the economically and medically dis-  
1365 advantaged must be recognized. Special attention is also required for those who can-  
1366 not give or refuse consent for themselves, for those who may be subject to giving  
1367 consent under duress, for those who will not benefit personally from the research and  
1368 for those for whom the research is combined with care.
- 1369 9. Research Investigators should be aware of the ethical, legal and regulatory require-  
1370 ments for research on human subjects in their own countries as well as applicable in-  
1371 ternational requirements. No national ethical, legal or regulatory requirement should

1372 be allowed to reduce or eliminate any of the protections for human subjects set forth  
1373 in this Declaration.

1374 **B. BASIC PRINCIPLES FOR ALL MEDICAL RESEARCH**

- 1375 10. It is the duty of the physician in medical research to protect the life, health, privacy,  
1376 and dignity of the human subject.
- 1377 11. Medical research involving human subjects must conform to generally accepted sci-  
1378 entific principles, be based on a thorough knowledge of the scientific literature, other  
1379 relevant sources of information, and on adequate laboratory and, where appropriate,  
1380 animal experimentation.
- 1381 12. Appropriate caution must be exercised in the conduct of research which may affect  
1382 the environment, and the welfare of animals used for research must be respected.
- 1383 13. The design and performance of each experimental procedure involving human sub-  
1384 jects should be clearly formulated in an experimental protocol. This protocol should  
1385 be submitted for consideration, comment, guidance, and where appropriate, approval  
1386 to a specially appointed ethical review committee, which must be independent of the  
1387 investigator, the sponsor or any other kind of undue influence. This independent  
1388 committee should be in conformity with the laws and regulations of the country in  
1389 which the research experiment is performed. The committee has the right to monitor  
1390 ongoing trials. The researcher has the obligation to provide monitoring information to  
1391 the committee, especially any serious adverse events. The researcher should also  
1392 submit to the committee, for review, information regarding funding, sponsors, institu-  
1393 tional affiliations, other potential conflicts of interest and incentives for subjects.
- 1394 14. The research protocol should always contain a statement of the ethical considerations  
1395 involved and should indicate that there is compliance with the principles enunciated  
1396 in this Declaration.
- 1397 15. Medical research involving human subjects should be conducted only by scientific-  
1398 ally qualified persons and under the supervision of a clinically competent medical per-  
1399 son. The responsibility for the human subject must always rest with a medically quali-  
1400 fied person and never rest on the subject of the research, even though the subject has  
1401 given consent.
- 1402 16. Every medical research project involving human subjects should be preceded by care-  
1403 ful assessment of predictable risks and burdens in comparison with foreseeable bene-  
1404 fits to the subject or to others. This does not preclude the participation of healthy vol-  
1405 unteers in medical research. The design of all studies should be publicly available.
- 1406 17. Physicians should abstain from engaging in research projects involving human sub-  
1407 jects unless they are confident that the risks involved have been adequately assessed  
1408 and can be satisfactorily managed. Physicians should cease any investigation if the  
1409 risks are found to outweigh the potential benefits or if there is conclusive proof of  
1410 positive and beneficial results.
- 1411 18. Medical research involving human subjects should only be conducted if the im-  
1412 portance of the objective outweighs the inherent risks and burdens to the subject. This  
1413 is especially important when the human subjects are healthy volunteers.
- 1414 19. Medical research is only justified if there is a reasonable likelihood that the popula-  
1415 tions in which the research is carried out stand to benefit from the results of the re-  
1416 search.
- 1417 20. The subjects must be volunteers and informed participants in the research project.

21. The right of research subjects to safeguard their integrity must always be respected. Every precaution should be taken to respect the privacy of the subject, the confidentiality of the subject's information and to minimize the impact of the study on the subject's physical and mental integrity and on the personality of the subject.
22. In any research on human beings, each potential subject must be adequately informed of the aims, methods, sources of funding, any possible conflicts of interest, institutional affiliations of the researcher, the anticipated benefits and potential risks of the study and the discomfort it may entail. The subject should be informed of the right to abstain from participation in the study or to withdraw consent to participate at any time without reprisal. After ensuring that the subject has understood the information, the physician should then obtain the subject's freely-given informed consent, preferably in writing. If the consent cannot be obtained in writing, the non-written consent must be formally documented and witnessed.
23. When obtaining informed consent for the research project the physician should be particularly cautious if the subject is in a dependent relationship with the physician or may consent under duress. In that case the informed consent should be obtained by a well-informed physician who is not engaged in the investigation and who is completely independent of this relationship.
24. For a research subject who is legally incompetent, physically or mentally incapable of giving consent or is a legally incompetent minor, the investigator must obtain informed consent from the legally authorized representative in accordance with applicable law. These groups should not be included in research unless the research is necessary to promote the health of the population represented and this research cannot instead be performed on legally competent persons.
25. When a subject deemed legally incompetent, such as a minor child, is able to give assent to decisions about participation in research, the investigator must obtain that assent in addition to the consent of the legally authorized representative.
26. Research on individuals from whom it is not possible to obtain consent, including proxy or advance consent, should be done only if the physical/mental condition that prevents obtaining informed consent is a necessary characteristic of the research population. The specific reasons for involving research subjects with a condition that renders them unable to give informed consent should be stated in the experimental protocol for consideration and approval of the review committee. The protocol should state that consent to remain in the research should be obtained as soon as possible from the individual or a legally authorized surrogate.
27. Both authors and publishers have ethical obligations. In publication of the results of research, the investigators are obliged to preserve the accuracy of the results. Negative as well as positive results should be published or otherwise publicly available. Sources of funding, institutional affiliations and any possible conflicts of interest should be declared in the publication. Reports of experimentation not in accordance with the principles laid down in this Declaration should not be accepted for publication.

#### **C. ADDITIONAL PRINCIPLES FOR MEDICAL RESEARCH COMBINED WITH MEDICAL CARE**

28. The physician may combine medical research with medical care, only to the extent that the research is justified by its potential prophylactic, diagnostic or therapeutic

- 1464 value. When medical research is combined with medical care, additional standards  
1465 apply to protect the subjects who are research subjects.
- 1466 29. The benefits, risks, burdens and effectiveness of a new method should be tested  
1467 against those of the best current prophylactic, diagnostic, and therapeutic methods.  
1468 This does not exclude the use of conventional fatty acid supplementation, or no  
1469 treatment, in studies where no proven prophylactic, diagnostic or therapeutic method  
1470 exists.
- 1471 30. At the conclusion of the study, every subject entered into the study should be assured  
1472 of access to the best proven prophylactic, diagnostic and therapeutic methods identi-  
1473 fied by the study.
- 1474 31. The physician should fully inform the subject which aspects of the care are related to  
1475 the research. The refusal of a subject to participate in a study must never interfere  
1476 with the subject-physician relationship.
- 1477 32. In the treatment of a subject, where proven prophylactic, diagnostic and therapeutic  
1478 methods do not exist or have been ineffective, the physician, with informed consent  
1479 from the subject, must be free to use unproven or new prophylactic, diagnostic and  
1480 therapeutic measures, if in the physician's judgment it offers hope of saving life, re-  
1481 establishing health or alleviating suffering. Where possible, these measures should be  
1482 made the object of research, designed to evaluate their safety and efficacy. In all cas-  
1483 es, new information should be recorded and, where appropriate, published. The other  
1484 relevant guidelines of this Declaration should be followed.

1485

**APPENDIX 2****Appendix 2 - Doseringsschema av Studiepreparat**

Studiepreparat Formulaid™ 2:1 (ARA/DHA)

Beredning: Olja

Innehåll: Arachidonsyra (ARA) 240-290 mg/g (mean 265 mg/g)  
 Dokosahexaensyra (DHA) 120-150 mg/g (mean 135mg/g)

Densitet: 0,9 g/cm^3**Dosering av Formulaid™**

Måldos vid supplementering är: DHA 50 mg/kg/dag samt ARA 100 mg/kg/dag.

Administrering påbörjas vid det 2:a enterala målet efter födelsen och ges om möjligt vid samma tidpunkt varje dag.

Dosökning sker i steg av 0,1 ml enligt separat doseringsschema. Maximal dos är 1 ml/dygn.  
 Dosen beräknas på födelsevikt till dess att den aktuella vikten överskridit födelsevikten och därefter på aktuell vikt.

| Enteralt intag | Bröstmjölks och övriga modersmjölksersättningar | Enbart 100% PreNAN Discharge     |
|----------------|-------------------------------------------------|----------------------------------|
| Formulaid™ dos | 0,39 ml/kg/dygn 1 gång dagligen.                | 0,33 ml/kg/dygn 1 gång dagligen. |

|                | Viktgräns (g) för dosökning                                                  |                                                |
|----------------|------------------------------------------------------------------------------|------------------------------------------------|
| Formulaid (ml) | Nutrieras med bröstmjölks, övriga ersättningar eller delvis PreNAN Discharge | Nutrieras med enbart med 100% PreNAN Discharge |
| 0,1            | 260 g                                                                        | -                                              |
| 0,2            | 520 g                                                                        | -                                              |
| 0,3            | 780 g                                                                        | -                                              |
| 0,4            | 1040 g                                                                       | 1215 g                                         |
| 0,5            | 1300 g                                                                       | 1520 g                                         |
| 0,6            | 1560 g                                                                       | 1825 g                                         |
| 0,7            | 1820 g                                                                       | 2130 g                                         |
| 0,8            | 2080 g                                                                       | 2435 g                                         |
| 0,9            | 2340 g                                                                       | 2740 g                                         |
| 1,0            | 2600 g                                                                       | 3045 g                                         |

## APPENDIX 3

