### Preterm Child – Treated

All infants will receive parenteral and enteral nutrition according to clinical practice and routines.

The group of infants randomized to treatment with enteral Formulaid™ will receive AA and DHA with a quotient that is 2:1. The time period for the enteral supplementation will start during the first day of life until 40 weeks postmenstrual age. The dose given will be 100 mg AA/kg/day and 50 mg DHA/kg/day, i.e. with volumes ranging from 0.1 ml to 1 ml/day (see Appendix A for details in dosing).

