## 3.3 Safety Variables

### 3.3.1 Exposure and Compliance of Study Drug

Exposure will be described as per following for the treated group:

- Number of days in study that infants have been exposed to IP
- Mean daily dose of AA mg/kg/day and DHA mg/kg/day. (They are expected to be 100 and 50 mg/kg/day, respectively at the beginning of the study. Dose adjustment were to be performed after the infant has regained its birthweight and weight gain results in an increase of 0.1 ml or more.)

Compliance will be described as percentage of number of days IP received / total number of days in study \* 100.

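### Appendix 2's ml/kg figure and weight table do not give the stated 100 mg AA and 50 mg DHA per kg per day, and the SAP has no rule for computing the dose delivered

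*Combined protocol and SAP*

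**What the plan says.** The synopsis, protocol section 4 (arm B) and SAP 1.3 give the supplement as 100 mg AA and 50 mg DHA per kg per day. Protocol 6.2 puts it as what infants will get: "The dose given will be 100 mg AA/kg/day and 50 mg DHA/kg/day". Appendix 2, in Swedish, calls it a target: "Måldos vid supplementering är: DHA 50 mg/kg/dag samt ARA 100 mg/kg/dag".

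Appendix 2 then gives the figures that turn the target into a volume:

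- AA content: "Arachidonsyra (ARA) 240-290 mg/g (mean 265 mg/g"), and DHA content: "Dokosahexaensyra (DHA) 120-150 mg/g (mean 135mg/g").
- Density: "Densitet: 0,9 g/cm" cubed.
- Volume for infants on breast milk or other formula: "0,39 ml/kg/dygn 1 gång dagligen".
- A table of weight limits for dose increases in 0.1 ml steps. The main column runs from 0.1 ml at 260 g to 1.0 ml at 2600 g in equal 260 g intervals, with a maximum of 1 ml per day.
- Dosing on birth weight until current weight exceeds it, then on current weight.

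SAP 3.3.1 plans to report the mean daily AA and DHA dose in mg/kg/day and adds: "They are expected to be 100 and 50 mg/kg/day, respectively at the beginning of the study". It defines compliance by days: "Compliance will be described as percentage of number of days IP received / total number of days in study". The definitions appended to the SAP (item 2) set the per-protocol cut at compliance of at least 70%.

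**The concern.** The dose in mg/kg, the volume in ml/kg and the weight table are three statements of one quantity, and they should agree. They do not, and the table, which sets the volume at a given weight, is furthest from the stated dose. Its 0.1 ml step is large relative to the volume a very small infant receives, so the gap is widest at the lowest weights. Protocol section 4 plans 84 of the 210 infants at a gestational age of 24 weeks + 6 days or less.

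The SAP expects 100/50 at the beginning of the study, when infants are smallest. It does not say how ml become mg, which density and content to use, which weight goes in the denominator, or whether the mean is broken down by gestational age or time. If density were left out, or nominal figures used, the gap would not show. A single mean over the whole study would dilute an early shortfall.

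**Working it through.** **Inputs**, all from Appendix 2: density 0.9 g/ml; AA 265 mg/g (240 to 290); DHA 135 mg/g (120 to 150); 0.39 ml/kg/day; main-column limits every 260 g.

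**Content per ml at mean values.** AA: 0.9 × 265 = 238.5 mg/ml. DHA: 0.9 × 135 = 121.5 mg/ml.

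**Trying to reproduce 100/50 from 0.39 ml/kg.**

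- AA: 0.39 × 238.5 = 93.0 mg/kg. DHA: 0.39 × 121.5 = 47.4 mg/kg. These are 7% and 5% below the stated dose.
- Over the content range, AA: 0.39 × 0.9 × 240 = 84.2 to 0.39 × 0.9 × 290 = 101.8. DHA: 0.39 × 0.9 × 120 = 42.1 to 0.39 × 0.9 × 150 = 52.7.
- With density left out: 0.39 × 265 = 103.4 and 0.39 × 135 = 52.7.

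At mean content the stated dose is reached only if the appendix's own density is ignored.

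**Weight table, main column.** Each limit is where the next volume begins, so the dose per kg of dosing weight is volume × mg/ml ÷ weight. At every limit the volume is 0.1/0.260 = 0.385 ml/kg.

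| Dosing weight | Volume | AA, mg/kg | DHA, mg/kg |
|---|---|---|---|
| any limit (e.g. 520 g) | 0.385 ml/kg | 91.7 | 46.7 |
| 519 g | 0.1 ml | 23.85/0.519 = 46.0 | 12.15/0.519 = 23.4 |
| 779 g | 0.2 ml | 47.7/0.779 = 61.2 | 24.3/0.779 = 31.2 |
| 1039 g | 0.3 ml | 71.55/1.039 = 68.9 | 36.45/1.039 = 35.1 |
| 3000 g (at the 1 ml cap) | 1.0 ml | 238.5/3 = 79.5 | 121.5/3 = 40.5 |

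**Table against the appendix's own ml/kg.** At 519 g, 0.39 × 0.519 = 0.20 ml; the table gives 0.1 ml.

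**Average over a weight range.** The documents give no weight distribution, so an even spread is assumed. Over 500 to 1000 g the mean is mg/ml × [0.1 ln(520/500) + 0.2 ln(780/520) + 0.3 ln(1000/780)] ÷ 0.5. The bracket is 0.0039 + 0.0811 + 0.0745 = 0.1596. AA: 238.5 × 0.1596/0.5 = 76.1. DHA: 121.5 × 0.1596/0.5 = 38.8. The same calculation gives 75.0/38.2 over 400 to 1300 g and 82.9/42.2 over 520 to 2600 g.

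**Effect of dosing on birth weight.** The documents give no weight-loss figure, so 0 to 10% is assumed. Birth weight 780 g (0.3 ml): 91.7 mg AA per current kg with no loss, 71.55/0.702 = 101.9 with 10% loss. Birth weight 519 g (0.1 ml): 46.0 with no loss, 23.85/0.467 = 51.1 with 10% loss.

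**The case against.** Appendix 2 calls 100/50 a target and the 0.1 ml steps are disclosed, so some rounding is to be expected. For the ml/kg figure alone the gap is 5 to 7%, and 100/50 lies inside the stated content range. The low values at 519 and 779 g are troughs of a sawtooth: one gram more and the infant is back at 91.7. They also depend on reading the table as rounding down. If volumes instead followed 0.39 ml/kg rounded to the nearest 0.1 ml, mean AA over evenly spread weights from 500 to 2600 g would be 92.8. All of this is fair and limits the size of the point, but it does not remove the contradiction. The column is headed as limits for a dose increase, protocol section 4 raises the dose only once weight gain is worth 0.1 ml or more, and a table that differs twofold from the ml/kg figure beside it needs reconciling.

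Four stronger readings are tempting, and the documents do not support them.

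- A reader might infer that the trial would report a dose its infants did not receive. SAP 3.3.1 already plans to report mean mg/kg/day. What is missing is the conversion rule and the breakdown.
- A reader might infer that a null result could not be told apart from under-delivery. Serum AA and DHA are measured serially and are second and third in the confirmatory sequence (SAP 4.1, 4.6.2). A non-significant primary result stops formal testing, but the estimates and intervals remain. A pharmacokinetic analysis also follows the first 10 subjects.
- A reader might infer that every infant is always below 100 mg AA/kg. At mean content that holds per kg of dosing weight; per kg of current weight it can fail during early weight loss, as shown above.
- A reader might want the 70% per-protocol cut put on delivered amount. Measured against 100 mg/kg, that would exclude fully adherent treated infants by weight: 0.1 ml gives under 70 mg/kg from 341 g (23.85/0.341 = 69.9) to 519 g, and 0.2 ml from 682 g (47.7/0.682 = 69.9) to 779 g. Weight is related to ROP risk, so the exclusions would not be neutral.

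**Conclusion.** The dose figures contradict each other and must be reconciled. At mean content and the stated density, the ml/kg figure is 7% (AA) and 5% (DHA) below 100/50. The main-column table is at least 8% and 7% below per kg of dosing weight, and just under 520 g it is about half the stated dose. Assuming an even spread over 500 to 1000 g, the average shortfall is about 24% for AA and 22% for DHA; a real weight distribution would change this. The table results rest on reading the limits as the start of each step.

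The column for infants fed only PreNAN Discharge (0.33 ml/kg) is not judged. The oil alone gives 78.7/40.1 there, but protocol section 2 says these lipids are included in preterm formula and no content for that product is given.

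The consequence is one of exposure reporting: the SAP's expected figure does not follow from the schedule, and its planned summary is not specified well enough to show the difference reliably.

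**What to change.** - **Reconcile.** The clinical team should bring the stated dose (synopsis, protocol 4 and 6.2, SAP 1.3) into agreement with Appendix 2's ml/kg figure and weight table. This review takes no position on which is right. The references to Appendix A should also point to the schedule, which is titled Appendix 2.
- **SAP 3.3.1, expected dose.** Correct the expectation of 100 and 50 to match the reconciled schedule.
- **SAP 3.3.1, derivation.** Compute the planned mean daily mg/kg/day as volume given × stated density × stated content ÷ weight. Say whether the weight is dosing weight or current weight; showing both is easy. Summarise by gestational age stratum and postnatal week so that an early shortfall in the smallest infants is visible.
- **Per-protocol population.** Keep the 70% cut on days received. Amount delivered relative to the schedule may be shown descriptively beside it.

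The cost is wording and a small derived variable. Weight is measured weekly. Protocol 10.9 has drug administration recorded on the CRF but does not say that daily volume is captured; where it is not, volume would have to be inferred from the schedule and weight, and the report should say so. The reported dose may look less favourable than 100/50.
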